##### Factorial analysis for synergistic effects

2.9.1.3

To directly address the study’s aim of elucidating synergistic mechanisms and to capitalize on the robust factorial design, a 2 × 2 factorial analysis will be nested within the models. The main effect of the rTMS factor (active vs. sham), the main effect of the DMI factor (active vs. sham), and the rTMS × DMI interaction effect on the primary outcome will be tested. A statistically significant positive interaction term will quantitatively support the hypothesis that the combined intervention produces benefits exceeding the additive effects of the individual modalities.

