The cognitive demands inherent in learning and performing dance routines, such as memorizing steps, coordinating movements, and adapting to music, provide an ideal environment for cognitive rehabilitation. Combined with the targeted neural modulation from rTMS, which can enhance neural efficiency and connectivity in critical cognitive regions, this may yield more profound and lasting improvements in specific cognitive domains (e.g., executive function, memory, attention) and overall global cognition in MCI patients (Quan et al., 2025; Yuan et al., 2025). The engaging and enjoyable nature of dance may further improve adherence to rTMS sessions, maximizing the therapeutic benefits of both interventions. The combined intervention offers a comprehensive approach by simultaneously targeting the neurological underpinnings of MCI through rTMS and addressing the physical, cognitive, social, and emotional dimensions through dance—a multi-modal framework essential for managing a condition as complex as MCI, which affects multiple aspects of an individual’s well-being.

Despite the compelling theoretical rationale for combining rTMS and dance, randomized controlled trials investigating their synergistic effects in older adults with MCI remain scarce. Existing research has largely focused on the individual effects of rTMS or various forms of exercise, including dance, but rarely on their combined impact using a robust factorial design. To our knowledge, no randomized controlled double-blind study has compared rTMS combined with Chinese square dance against appropriate controls, nor comprehensively disentangled the individual contributions of each modality. Therefore, the primary aim of this study is to evaluate the clinical efficacy of combined rTMS and Chinese square dance on cognitive function, neuroplasticity, and physical performance in older adults with MCI. Secondary aims include evaluating the individual effects of rTMS and Chinese square dance and elucidating the potential synergistic mechanisms underlying the combined intervention, thereby providing a robust rationale for future therapeutic strategies in MCI. **Figure 1** illustrates the proposed biological framework of this combined intervention, summarizing the four shared neurobiological pathways—BDNF signaling, cortical excitability, motor-cognitive integration, and neuroplasticity—on which rTMS and DMI are hypothesized to converge to enhance cognitive outcomes in MCI.

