#### Neurophysiological biomarkers

2.4.3

To objectively quantify changes in neuroplasticity and cognitive processing speed, the P300 event-related potential (ERP) will be recorded using electroencephalography (EEG) at baseline (T0) and post-intervention (T1). The P300 component will be elicited using a standardized two-stimulus auditory oddball paradigm, in which participants are instructed to press a button in response to an infrequent target tone (e.g., 2000 Hz, 20% probability) embedded within a series of frequent standard tones (e.g., 1000 Hz, 80% probability) (Costanzo et al., 2024).

The P300 is a robust, non-invasive biomarker of attention and working memory updating. In individuals with MCI, the P300 typically exhibits reduced peak amplitude and prolonged latency compared to healthy age-matched controls, reflecting slowed neural processing and reduced allocation of attentional resources (Demirayak et al., 2023). We will specifically analyze the P300 peak latency (in milliseconds) and peak amplitude (in microvolts) at midline electrodes (Fz, Cz, Pz), where the signal is most prominent. A reduction in P300 latency and an increase in amplitude post-intervention will serve as direct neurophysiological evidence of enhanced cortical efficiency and target engagement by the iTBS and dance interventions (Stuckenschneider et al., 2020).

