##### Analysis of primary and secondary outcomes

2.9.1.2

To evaluate the individual and synergistic effects of the interventions across the three assessment time points (baseline, Week 12, and Week 24), linear mixed-effects models (LMMs) will be employed. LMMs are particularly well-suited to this trial design, as they accommodate repeated measures, account for intra-subject correlation, and appropriately handle missing data under the missing-at-random (MAR) assumption without necessitating listwise deletion. The outcome measures—including global cognitive function (MoCA), memory, executive function, EEG/ERP parameters, and physical performance metrics—will be modelled as dependent variables. Fixed effects will comprise Group (Combined Intervention, rTMS Only, DMI Only, Control), Time (T0, T1, T2), and the Group × Time interaction term, with the latter serving as the primary indicator of intervention efficacy over the study period. Participant identification will be specified as a random intercept to account for between-subject variability.

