### Insights from previous studies on behavioral symptoms and engagement

3.2

Apathy is a clinically meaningful target in MCI, as reduced motivation may limit participation in lifestyle interventions. iTBS over the left DLPFC has been reported to improve both global cognition and neuropsychiatric symptoms in MCI (Chu et al., 2021; Han et al., 2026). We hypothesize that, if present, rTMS-induced improvements in motivation and drive may support higher adherence to subsequent DMI sessions; this mediation effect will be interpreted cautiously given the sample size.

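### The mechanism aim has a named synergy test on MoCA only; P300 and rs-fMRI have none, P300 change is read without a comparator, and the motivation mediator is not measured

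*Protocol article*

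**What the plan says.** The Introduction lists among the secondary aims "elucidating the potential synergistic mechanisms underlying the combined intervention". Section 2.9.1.3 presents the factorial analysis as the answer: "To directly address the study’s aim of elucidating synergistic mechanisms and to capitalize on the robust factorial design". The same section then limits the test: "the rTMS × DMI interaction effect on the primary outcome will be tested". The primary outcome is the T0 to T1 change in MoCA (sections 2.4.1 and 2.10).

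The protocol collects two mechanism markers at T0 and T1: P300 (section 2.4.3) and rs-fMRI connectivity (section 2.4.4).

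- **P300 in the analysis sections.** Section 2.9.1.2 includes it in the mixed models: "memory, executive function, EEG/ERP parameters, and physical performance metrics—will be modelled as dependent variables". The fixed effects are four-level Group, Time "and the Group × Time interaction term, with the latter serving as the primary indicator of intervention efficacy over the study period". Section 2.10 makes P300 change one of three key secondary outcomes under Holm-Bonferroni.
- **P300 in the outcome section.** Section 2.4.3 says: "A reduction in P300 latency and an increase in amplitude post-intervention will serve as direct neurophysiological evidence of enhanced cortical efficiency". The sentence goes on to count the change as target engagement by both interventions. It names no comparison arm.
- **rs-fMRI.** It is not among the outcomes listed in section 2.9.1.2. Section 2.10 classes it as supportive or exploratory.
- **Mediation.** Section 3.2 supposes that rTMS may raise motivation and so improve dance adherence, and adds that "this mediation effect will be interpreted cautiously given the sample size". Table 1 has no row for motivation or apathy, and none for BDNF or cortical excitability. The last two are among the four shared pathways named in the Introduction and Figure 1.

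**The concern.** The aim concerns how the two interventions work together, and the only named synergy test is on a clinical score. A positive rTMS × DMI term on MoCA says that the joint benefit exceeds the sum of the two. It would look the same whatever pathway produced it.

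The markers that could speak to mechanism are covered by an omnibus test that answers a different question, and by a sentence that treats a change over time as evidence in itself. Two misreadings are then open to the eventual report. A significant Group × Time term for P300 could be presented as synergy when the effects simply add. A P300 shift in an active arm could be credited to iTBS and dance when the sham/social arm shows the same shift from repeat testing. Separately, a mediation result is anticipated for which the mediator will not have been recorded.

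**Working it through.** **1. The plan's own figure.** Section 2.7 gives 128 participants (32 per group) for f = 0.25, power 0.80 and alpha 0.05, inflated to 160 for 20% attrition. For a 1-df effect in a four-cell design, take a noncentral F with noncentrality λ = f²N and N − 4 error df. With N = 128, λ = 0.0625 × 128 = 8 and power is 0.801. Then 128/0.80 = 160. Both figures reproduce for a 1-df factorial effect, so the same formula is used below.

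**2. Does the Group × Time test on P300 isolate synergy?** P300 is measured at T0 and T1 only, so with four arms the term has 3 df and compares T0–T1 change across arms. Assume each factor shifts that change by d SD with no interaction (d is an assumption; the protocol gives no P300 effect size).
- Arm means are 2d, d, d and 0. The grand mean is d, and the deviations are d, 0, 0 and −d.
- f² = (d² + d²)/4 = d²/2.
- d = 0.5: f² = 0.125, λ = 128 × 0.125 = 16, power on 3 and 124 df = 0.93.
- d = 0.3: f² = 0.045, λ = 5.76, power = 0.49.

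So the stated indicator would be significant in about 93% or 49% of trials in which the true rTMS × DMI interaction is exactly zero. It is a valid test that the arms differ, but not a test of synergy.

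**3. What would the 1-df contrasts deliver on P300?**
- *Interaction.* The contrast is a difference of differences, D, in SD units of change. With n per arm its standard error is √(4/n) SD. At n = 32 this is √(4/32) = 0.354 SD, so the 95% half-width is about 1.98 × 0.354 = 0.70 SD. Here f = D/4.
  - D = 1.0: f = 0.25 and power is 0.80, or 0.66 at the first Holm step (0.05/3).
  - D = 0.5: f = 0.125, λ = 0.015625 × 128 = 2, and power is 0.29, or 0.16 at the first Holm step.
- *Main effects.* Active v sham, and DMI v social control, each compare 64 with 64. A 0.5 SD difference corresponds to f = 0.25, with power 0.80 at alpha 0.05.

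The target-engagement contrasts are therefore reasonably informative at 0.5 SD, while the interaction is not.

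**4. Sections set side by side.** Section 2.9.1.2 judges P300 by a comparison across randomized arms. Section 2.4.3 judges it by the direction of change after the intervention. A fall in latency and a rise in amplitude of similar size in all four arms would meet the wording of the second and give nothing on the first. The protocol does not say that the first governs.

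**5. The mediation.** Its path runs from rTMS to motivation to DMI adherence. The first and last are available: rTMS is randomized, and attendance is recorded session by session in the DMI log (section 2.3.2). The middle term has no scheduled measure. The obstacle is therefore not sample size, which is the reason section 3.2 gives for caution.

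**The case against.** The strongest reply is that P300 already has a controlled analysis. It is in the four-arm model, which section 2.9.1.2 introduces as covering both individual and synergistic effects, and its inference rests on Holm-adjusted p-values. The rTMS × DMI contrast is a linear combination of the Group × Time terms already fitted. Naming the interaction for the primary outcome alone limits multiplicity, and an article may leave contrasts for secondary outcomes to a fuller document. Section 2.4.3 can be read as merely giving the favourable direction. Section 3.2 is discussion text, and no mediation model appears in section 2.9. Nor must a trial assay every pathway in its rationale.

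Much of this stands. A reader might infer that nothing planned bears on mechanism, or that synergy on P300 could not be tested. The documents support neither. Between-arm P300 and rs-fMRI results bear on neuroplasticity, one of the four named pathways, and the contrast can be formed from the fitted model. A reader might also take section 2.4.3 as declaring success whenever sample means move the right way. No passage does that.

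The reply does not dispose of the rest. The article does not merely omit the contrast: the one sentence that names it ties it to MoCA while claiming to address mechanisms. The stated P300 indicator can be significant under pure additivity. The wording of section 2.4.3 calls an uncontrolled change direct evidence.

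**Conclusion.** The concern holds in limited form, as a mismatch between the mechanism aim and the tests named for it. It does not put the primary MoCA analysis in doubt. Three statements need correcting: the claim that a MoCA interaction addresses mechanism, the comparator-free reading of P300, and the reference to a mediation effect without a measured mediator.

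The size depends on assumed effects. With 128 completers, the omnibus P300 test is significant in about 93% of trials under additive shifts of 0.5 SD per factor, and about 49% under 0.3 SD, with no synergy present. A named interaction contrast would have power of about 0.29 for 0.5 SD and 0.80 for 1.0 SD at alpha 0.05. These figures assume 32 completers per arm, equal variances, and a simple analysis of T0–T1 change. The arguments about section 2.4.3 and section 3.2 rest on wording alone and need no figure.

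**What to change.** 1. In section 2.9.1.3, extend the rTMS, DMI and rTMS × DMI contrasts to T0–T1 change in P300 and in DMN and frontoparietal connectivity, and name rs-fMRI among the modelled outcomes. Label the marker interactions supportive and report them with confidence intervals, because they will be imprecise. Say that the MoCA interaction tests non-additivity of the clinical effect.
2. In section 2.4.3, define target engagement by iTBS as the active v sham difference in P300 change, target engagement by dance as the DMI v social control difference, and synergy as the interaction. Keep lower latency and higher amplitude as the favourable directions.
3. In section 3.2, replace the mediation by the comparison of DMI attendance in Combined v DMI Only. This is randomized and estimable from the session log. It would show whether active rTMS affects attendance, not whether motivation is the route. State that BDNF and cortical excitability are background hypotheses which the trial does not test.

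The cost is protocol wording and a few more contrasts on data already being collected, with no new assessments. The downside is narrower mechanistic claims and some additional supportive estimates with wide intervals.

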##### Covariates and adjustments for multiplicity

2.9.1.4

The models will be adjusted for pre-specified, clinically relevant covariates, including age, gender, educational attainment, and baseline MoCA scores. Should baseline imbalances be detected across groups despite randomization, the affected variables will additionally be incorporated as covariates. For multiple pairwise comparisons across groups or time points, *post-hoc* analyses will be adjusted using either the False Discovery Rate (FDR) method or the Bonferroni correction to control the family-wise error rate.

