### Participants

2.2

Participants will be recruited from the Department of Rehabilitation at Handan Central Hospital. A convenience sampling method will be employed, with local physicians providing a list of potentially eligible patients diagnosed with MCI. All participants will provide written informed consent before enrollment. A family member or legal guardian will also be asked to co-sign the consent form. Participant data will be anonymized to ensure confidentiality. The data will be secured during the study and destroyed five years after the study completion.

Inclusion criteria: (1) Diagnosis of amnestic or multi-domain MCI by a specialist physician according to the National Institute on Aging-Alzheimer’s Association (NIA-AA) criteria. (2) Age between 50 and 85 years. (3) Montreal Cognitive Assessment (MoCA) score between 18 and 25. (4) Geriatric Depression Scale (GDS-15) score < 5. (5) Physically able to participate in dance activities without assistive devices and deemed at low risk for falls (Berg Balance Scale score ≥ 41). (6) Stable doses of any prescribed medications for at least 30 days prior to screening. (7) Sufficient visual and auditory acuity (with correction if necessary) to complete assessments and interventions. (8) Voluntarily agrees to participate and provides informed consent.

Exclusion criteria: (1) Diagnosis of dementia (any type). (2) Presence of major psychiatric conditions (e.g., major depressive disorder, schizophrenia) or neurological disorders (e.g., Parkinson’s disease, stroke) that could confound cognitive assessment. (3) Contraindications to rTMS (e.g., history of seizures, metallic implants in the head). (4) Regular participation in structured exercise (≥ 3 times per week) or another cognitive intervention program within the past six months. (5) Abuse of drugs or alcohol that could cause cognitive impairment.

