### Measurement outcomes

2.4

Assessments will be conducted at three time points: Baseline (T0), Post-Intervention (T1, Week 12), and Follow-up (T2, Week 24). T1 assessments will be conducted 24–72 hours after the final intervention session of Week 12, to avoid the potential confounding influence of acute rTMS and dance exposure on cognitive and physical performance. To control for circadian variation, T1 and T2 assessments for each participant will be scheduled at the same time of day as that participant’s T0 assessment. Participants’ self-rated scales will be completed under guidance. All the tests will be administered in accordance with the standard procedures. The specific schedule of enrolment, interventions, and assessments is detailed in **Table 1**.

**Table 1 T1:** SPIRIT schedule of enrolment, interventions, and assessments.

Procedure	*Enrolment*	*Allocation*	*Intervention Phase*	*Post-Intervention*	*Follow-up*
*Timepoint*	-t_1_ (Screening)	T0 (Baseline)	Weeks 1–12	T1 (Week 12)	T2 (Week 24)
Enrolment:					
*Eligibility Screening*	**X**				
*Informed Consent*	**X**				
*Demographics & Medical History*	**X**				
*Inclusion MoCA, GDS-15, BBS*	**X**				
*Randomization*		**X**			
Interventions:					
*Active or Sham iTBS (rTMS)*			**X**		
*Chinese Square Dancing (DMI)*			**X**		
*Social Activity Control*			**X**		
Assessments:					
Primary outcome					
*Montreal Cognitive Assessment (MoCA)*		**X**		**X**	**X**
Secondary outcomes					
*Wechsler Memory Scale (WMS-IV)*		**X**		**X**	**X**
*Trail Making Test (Part A & B)*		**X**		**X**	**X**
*Berg Balance Scale (BBS)*		**X**		**X**	**X**
*6-Minute Walk Test (6MWT)*		**X**		**X**	**X**
*12-item Short Form Survey (SF-12)*		**X**		**X**	**X**
Neurophysiological & exploratory					
*EEG/ERP (P300 Oddball paradigm)*		**X**		**X**	
*Resting-State fMRI (rs-fMRI)*		**X**		**X**	
Safety & fidelity					
*Adverse Events Monitoring*			**X**	**X**	
*Blinding Integrity Questionnaire*				**X**	
*Qualitative Interviews*					**X**

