-t₁: Initial screening phase to determine clinical eligibility based on MoCA, Geriatric Depression Scale (GDS-15), and Berg Balance Scale (BBS) inclusion criteria. T0: Baseline assessment conducted immediately prior to randomization. T1: Primary endpoint assessment conducted immediately following the 12-week intervention. T2: Follow-up assessment conducted 12 weeks post-intervention to determine durability of effects. MoCA, Montreal Cognitive Assessment; GDS-15, 15-item Geriatric Depression Scale; WMS-IV, Wechsler Memory Scale Fourth Edition; BBS, Berg Balance Scale; 6MWT, 6-Minute Walk Test; SF-12, 12-item Short Form Health Survey; EEG/ERP, Electroencephalography/Event-Related Potential; rs-fMRI, Resting-state Functional Magnetic Resonance Imaging.

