### Outcome hierarchy and multiplicity adjustment

2.10

To address concerns about multiplicity, the trial outcomes are organized in a pre-specified hierarchy. The primary outcome is the change from baseline (T0) to post-intervention (T1) in MoCA total score. Three pre-specified key secondary outcomes, all analyzed as T0 to T1 changes paralleling the primary, are: (1) change in executive function, operationalized as the TMT-B/A ratio to control for motor speed, with TMT-B and TMT-A reported separately as supporting analyses; (2) change in P300, assessed by peak latency (ms) and peak amplitude (μV) at midline electrodes (Fz, Cz, Pz); and (3) change in BBS score. To control the family-wise Type I error rate across these three key secondary outcomes, the Holm-Bonferroni step-down procedure will be applied; effect estimates with 95% confidence intervals (unadjusted and adjusted) will be reported, with the adjusted p-values used for inference. T0 to T2 changes (durability) for all three key secondary outcomes, as well as all other pre-specified outcomes—including WMS-IV (memory), 6MWT (functional exercise capacity), SF-12 (quality of life), and rs-fMRI (DMN and frontoparietal connectivity)—are treated as supportive/exploratory and are interpreted with caution.

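### The efficacy model leaves out the screening MoCA, a second pre-randomisation reading of the primary outcome: a modest loss of precision, not a bias

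*Protocol article*

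**What the plan says.** **Two readings before allocation.** In Table 1 (section 2.4), the enrolment column has a row "Inclusion MoCA, GDS-15, BBS". A separate row lists MoCA as the primary outcome at T0, T1 and T2. The legend describes the first occasion as "Initial screening phase to determine clinical eligibility based on MoCA, Geriatric Depression Scale (GDS-15), and Berg Balance Scale (BBS) inclusion criteria" and places the second before allocation: "T0: Baseline assessment conducted immediately prior to randomization". Section 2.2 gives the entry rule: "Montreal Cognitive Assessment (MoCA) score between 18 and 25".

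**One reading in the model.** Section 2.10 states that "The primary outcome is the change from baseline (T0) to post-intervention (T1) in MoCA total score". The linear mixed model in section 2.9.1.2 has a random intercept, and its fixed effects include "Time (T0, T1, T2), and the Group × Time interaction term, with the latter serving as the primary indicator of intervention efficacy". There is no screening time point. Section 2.9.1.4 adds: "The models will be adjusted for pre-specified, clinically relevant covariates, including age, gender, educational attainment, and baseline MoCA scores". No section gives the screening MoCA a role beyond eligibility.

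**The concern.** A single MoCA carries measurement error. A second reading taken before allocation helps to separate a participant's level from that error, so it can predict T1 beyond what T0 predicts. Because it precedes randomisation, it can be adjusted for without bias. If the two readings are separate administrations, the screening score exists for every randomised participant.

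What is at stake is the precision of the T0-to-T1 MoCA contrasts. These include the rTMS × DMI interaction in section 2.9.1.3, which carries the trial's claim of synergy.

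**Working it through.** **Inputs from the article:** 128 evaluable and 160 recruited, f = 0.25, power 0.80, alpha 0.05, 20% attrition (section 2.7); MoCA 18 to 25 at entry (section 2.2); model times T0, T1, T2 with a random intercept (section 2.9.1.2).

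**Assumed, because the article gives none:** correlations between MoCA readings, MoCA standard deviations and measurement error.

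**1. The plan's own figure.** Take a 1-df F test with four groups and noncentrality N × f² = 128 × 0.0625 = 8. Power is 0.801, and 128 / 0.8 = 160. The stated numbers reproduce as a 1-df factorial test. Section 2.7 labels the calculation differently, which is a separate matter.

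**2. Gain in a T1 analysis conditional on T0.** Let ρ be the correlation of each pre-randomisation reading with T1, and r the correlation between those two readings. Residual variance, as a share of the T1 variance, is:

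- T0 only: 1 − ρ²
- T0 and screening: 1 − 2ρ²/(1 + r)

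| ρ | r | T0 only | Both | Ratio |
|---|---|---|---|---|
| 0.5 | 0.9 | 0.750 | 0.737 | 0.982 |
| 0.7 | 0.8 | 0.510 | 0.456 | 0.893 |
| 0.8 | 0.8 | 0.360 | 0.289 | 0.802 |

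At the central row, 128 × 0.893 = 114.3, so about 115 evaluable participants give the power that 128 give with T0 alone. Equivalently, power at 128 rises from 0.80 to about 0.84, with f = 0.25 read on the one-baseline residual scale. In 1,500 simulated trials at these values, the empirical variance of the interaction estimate fell from 0.457 to 0.407, a ratio of 0.89.

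**3. Allowing for selection on screening 18 to 25.** Selection narrows the screening score and reduces the gain. With whole-point scores, true-score SD 2 to 3, error SD 1.5 to 2 and extra true-change SD 0 to 1, residual variance fell from 3.77 to 3.31 (12%) in the best scenario and from 6.82 to 6.43 (6%) in the worst. Repeat runs on similar values gave cuts between 5% and 13%.

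**4. Less favourable assumptions on the same grid:**

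- age and education already explain 30% of true-score variance: 4% to 12%
- screening error one-third larger than T0 error: 3% to 8%
- error correlation of 0.3 between the two readings: 4% to 10%
- 30% explained, error one-third larger and error correlation 0.2 together: 1% to 5%

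As a cross-check without selection, suppose screening correlates 0.6 with T1, T0 correlates 0.7 with T1, and r = 0.8. The squared partial correlation is (0.6 − 0.7 × 0.8)² / [(1 − 0.49)(1 − 0.64)] = 0.0016 / 0.1836 = 0.009, so the gain is about 1%.

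**5. In participants.** A 1% cut is worth 128/0.99 − 128 = 1.3 evaluable participants. A 12% cut is worth 128/0.88 − 128 = 17.5.

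**6. The model as written.** With T0 an unconstrained response and complete data, the T0-to-T1 Group × Time estimate is a comparison of change scores.

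- *Screening as a time-constant covariate.* It cancels. In a simulated trial of 160, the interaction at T1 was 1.394 (SE 0.692) with no MoCA covariate, with T0, and with T0 plus screening.
- *Screening × Time.* Write screening = τ + eₛ, T0 = τ + e₀ and T1 = τ + δ + e₁. The change is δ + e₁ − e₀. If errors are independent and true change is unrelated to level, this is uncorrelated with screening. Simulated correlations were −0.0003 to 0.001. In three simulated trials the SE without and with the term was 0.753 and 0.752, 0.777 and 0.776, 0.765 and 0.764.
- *If change is related to level.* When ρ < r, the term recovers something: at ρ = 0.7 and r = 0.8, a share of (0.7 − 0.8)² / [2 × (1 − 0.7)] = 1.7%. It never beats conditioning on T0 alone, because [2(1 − ρ) − (r − ρ)²] − (1 − ρ²) = (1 − ρ)² − (r − ρ)², which is not negative for r between ρ and 1.

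**The case against.** The strongest reply is that nothing here is wrong. Adjusting for one baseline reading is standard and unbiased. The covariate list is introduced with a word that leaves it open, and a further precision covariate is something an unseen analysis plan could add. This stands as far as validity goes, and it limits the weight of the point. It does not remove it: the article fixes the outcome times and names its MoCA covariate, and an extra covariate helps only if it is specified before the data are seen.

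A second reply is that the gain does not come free. It depends on how T0 enters the model. Section 2.9.1.2 makes T0 MoCA a response and section 2.9.1.4 makes it a covariate, and until that is settled, adding the screening score achieves essentially nothing. This stands in full. A reader might infer that lengthening the covariate list is enough; step 6 shows that it is not.

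A third reply is that 6% to 12% is a favourable range, since it assumes equally reliable readings with independent errors and no help from age or education. This also stands. The article gives neither the interval between screening and T0 nor who administers the screening test.

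A reader might also infer that the screening data are discarded or that the interaction is underpowered. The first overstates it, because the score decides eligibility. The second is not established here: 128 gives power 0.80 for a 1-df test at the planned f = 0.25.

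**Conclusion.** The point holds as a missed gain in precision. Two MoCA readings are scheduled before randomisation, and only T0 has a role in the efficacy model. The expected cut in residual variance is roughly 1% to 12% in a T1 analysis conditional on T0, or about 1 to 17 evaluable participants on top of 128.

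That range rests on assumed reliabilities. It sits at the low end if age and education already explain much of the true score, or if the screening reading is noisier than T0 or shares error with it. It is zero if the screening score is reused as T0. Reading the omission as a source of bias, or as a reason to doubt the trial's conclusions, is not supported: the analysis is valid without the screening score.

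**What to change.** 1. State in section 2.4 or Table 1 whether the screening and T0 MoCA are separate administrations. If the screening score is carried over as T0, say so; the remaining steps then fall away.
2. If they are separate, specify in sections 2.9.1.2 and 2.9.1.4 that the T1 MoCA analysis is conditional on T0 MoCA. Either T1 and T2 are the responses with T0 as a covariate, or T0 stays a response with pre-randomisation means constrained equal across arms.
3. Within that model, pre-specify screening MoCA as its own second baseline covariate. Do not average it silently with T0, because it has been selected to lie between 18 and 25.
4. The same may be done for BBS, a key secondary outcome that is also measured at screening and T0. No gain has been calculated for it.

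This needs no new data if the two administrations are separate. The cost is a rewording of the primary model, which is more than one extra item in a covariate list, and it must be done before outcome data are seen.
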